#### After regular completion of the trial

Patients may seek advice on the study or related issues after completion of the trial, but may be then referred to structures of regular health care (GPs, neurologists, psychiatrists, outpatient clinics, etc.) in case the scope of the issue is covered by standard of care.

## 9 Adverse Events

The following chapter contains the definitions of and procedures to assess and grade adverse events. Furthermore, it states the chain of report for severe or unexpected events.

### 9.1 Definitions

#### **Adverse Event - AE**

Any untoward medical or psychological occurrence temporally associated with the use of the intervention, but not necessarily causally related.

Every AE has to be rated concerning its severity:

- Mild: The AE is transient and easily bearable for the patient.
- Moderate: The AE causes inconveniences to the patient and interferes with his or her usual activities.
- Severe: The AE causes significant disturbances for the patient's usual activities.
- whether criteria of an SAE are fulfilled

Every AE has to be judged in terms of causal relation to the IMP:

- no causal relation  
The event is well understood and derives from another cause.
- possible causal relation  
An event with an understandable temporal relation to IMP application, well-fitting to a known pattern of reaction to the IMP, but easily attributable to several other factors.
- probable causal relation  
An event with an understandable temporal relation to IMP application, well-fitting to a known or expected pattern of reaction to the IMP. The event resolves after cessation of IMP application and is not explicable through other known factors of the patient's clinical condition.
- certain causal relation  
An event with an understandable temporal relation to IMP application, well-fitting to a known or expected pattern of reaction to the IMP. The event resolves after cessation of IMP application.

Documentation on MS relapse or progression and hospitalization due to MS relapse or progression should be made on the designated CRF-pages.

#### **Serious Adverse Event - SAE**

Every AE fulfilling any of the following criteria is considered an SAE:

- Suicidal ideation or intent (as measured by a score of 3 on BDI-II item 9 at any assessment, during the clinical interview at V2 or spontaneous report in a web message to the therapist or by contacting the study site)
- Hospitalization due to psychiatric disorder classified according to ICD10 or DSM5
- Lethal or life-threatening (incl. suicide or suicide attempt)

### **Suspected Unexpected Serious Adverse Reaction - SUSAR**

SUSARs are suspected unexpected serious adverse events, causally related to the application of the intervention. The following criteria have to be fulfilled:

- Type or severity of the event are not in accordance with the available information on the intervention.
- Lethal or life-threatening (incl. suicide or suicide attempt)

## **9.2 Documentation of AEs and SAEs**

Every AE has to be documented regardless of causal relationship. Documentation contains kind of event, start and duration, intensity and causal relationship. Related symptoms, clinical and laboratory findings should be summarized to a single AE. A sheet to document AEs is part of the CRF; furthermore, SAEs have to be separately documented on a distinct SAE sheet. If the necessary information is currently not available, follow-up reports have to be completed and transferred. In case of a lethal event, the autopsy report should ideally be included.

## **9.3 Chain of report for SAEs and SUSARs**

Obligations and deadlines given by the authorities remain untouched. This chapter is solely for the investigator's information.

| Table: Reports from Investigator to Principal Investigator |                                      |                                                          |
|------------------------------------------------------------|--------------------------------------|----------------------------------------------------------|
| Kind                                                       | Deadline                             |                                                          |
| AE                                                         | Upon completion of patient follow-up | Written report in CRF                                    |
| SAE                                                        | Within 15 days                       | Written report in CRF and on separate, distinct SAE form |

| Kind                                       | Deadline                   | Investigators |
|--------------------------------------------|----------------------------|---------------|
| SAE                                        | On Request                 |               |
| SUSAR                                      | Case report within 15 days | x             |
| SUSAR (Death)                              | Case report within 7 days  | x             |
| Follow-Up-Report (if initially incomplete) | After 8 days               | x             |

### Exceptions

The following SAEs should be excluded of the report chain in the course of this trial:

- SAEs occurring after trial inclusion but before treatment initiation
- Events with hospitalization planned before the inclusion to the trial

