## 6.6 Duration of trial participation for the individual subject

Prerequisites of trial completion for the individual subject

- Duration of treatment: 12 weeks
- Duration of follow-up: 1 year after study inclusion

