## **ADVANTAGES**

Participants will receive a novel online program to reduce depressive symptoms free of charge, either immediately or after waiting for 6 months (i.e. all patients will receive treatment). Participants may also benefit from a thorough clinical and psychological examination conducted at V1 and V2 by authorized personnel under the supervision of experienced clinicians.

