# **8 Discontinuation and Ongoing Treatment**

## **8.1 Premature discontinuation of participation for an individual subject**

### Reasons to discontinue participation (Criteria of discontinuation)

The following conditions are obligatory reasons to discontinue further participation in the trial according to the protocol:

- Decision of the patient
- Any further situation rendering further participation potentially harmful to the patient at the discretion of the investigator

The following conditions are possible reasons to discontinue further participation in the trial according to the protocol, and have to be reviewed as soon as possible by the principal investigator:

- Serious adverse event (SAE) and Suspected unexpected serious adverse reaction (SUSAR)
- Retrospectively assessed exclusion criterion

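### Read literally, the Section 9.3 exception takes the waitlist arm out of the 15-day SAE report to the principal investigator until month 6 (minor; wording fix)

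*Supplement*

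**What the plan says.** Four parts of the protocol bear on this.

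- **What counts as an SAE.** Section 9.1 includes "Suicidal ideation or intent (as measured by a score of 3 on BDI-II item 9 at any assessment", along with other routes of detection. No arm is singled out.
- **What must happen centrally.** Section 8.1 lists an SAE among the possible reasons to end participation, which "have to be reviewed as soon as possible by the principal investigator". The table in Section 9.3 gives the report that would prompt this review: from investigator to principal investigator within 15 days, as a "Written report in CRF and on separate, distinct SAE form".
- **What is exempt.** The exceptions in Section 9.3 remove "SAEs occurring after trial inclusion but before treatment initiation" from the report chain. There is no separate rule for the waitlist arm.
- **When the waitlist arm starts treatment.** Section 7 (Advantages) says participants receive the programme "either immediately or after waiting for 6 months (i.e. all patients will receive treatment").

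The adverse-event definition in Section 9.1 is also tied to programme use: "Any untoward medical or psychological occurrence temporally associated with the use of the intervention".

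**The concern.** In a drug trial, an exception for events before treatment starts usually covers a short gap between consent and first dose. Here one arm does not start for 6 months by design, so the same words reach far beyond a short gap. Suicidal ideation and intent is the safety concern that Section 7 names for this intervention. An investigator following Section 9.3 to the letter would send the 15-day report for a patient using the programme, and would have no duty to send it for a waitlist patient with the same finding. The stake is the completeness and symmetry of central safety reporting. The efficacy result is not at stake.

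**Working it through.** The check is mainly textual.

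**1. Does treatment include being on the waitlist?** The synopsis lists two treatments, Deprexis alone for 12 weeks and Deprexis with email support for 12 weeks. Waitlist stands in a separate row, as the control. Section 5 (Treatment) describes only versions of Deprexis. Section 7 says that all patients will receive treatment because the waitlist gets the programme later. On the protocol's own usage, a waitlist patient's treatment begins when programme access begins.

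**2. How long does the exception then last?**

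| Arm | Treatment starts | Period exempt from the SAE report chain |
|---|---|---|
| Deprexis | immediately | inclusion to programme start |
| Deprexis with email support | immediately | inclusion to programme start |
| Waitlist | after 6 months | inclusion to month 6, including weeks 0 to 12 |

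**3. How many patients?** The sample size section plans 100 per arm and allows for 20% dropout: 100 / (1 − 0.20) = 125 per arm, and 3 × 125 = 375, which reproduces the plan's total. The waitlist share is 125 / 375 = 33%. This only restates the 1:1:1 allocation; it says who is covered, not how many events are lost.

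**4. Does another provision restore the report?** Section 8.1 calls for prompt review but gives no notification route of its own. Under Section 9.3 the principal investigator documents the SAEs that have been reported. Section 9.2 requires a separate SAE sheet and Section 8.2 a detailed SAE assessment at the second clinical visit, but neither sets a deadline to the principal investigator. Section 11.1.1 has the coordinating centre check that procedures were followed after a suicidality SAE; it is stated for German sites only, without timing. None of these replaces the 15-day report.

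**5. How many events might be involved?** The documents give no rate for this SAE in a waitlist arm. Taking assumed risks up to month 6, the expected number is 125 × p and the chance of at least one is 1 − (1 − p)^125:

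| Assumed risk p | Expected waitlist SAEs | Chance of at least one |
|---|---|---|
| 0.5% | 0.6 | 47% |
| 1% | 1.3 | 72% |
| 2% | 2.5 | 92% |
| 5% | 6.3 | 99.8% |

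The lower rows are less plausible. Section 4.2 excludes moderate or high suicide risk, the BDI-II item 9 criterion needs the top score of 3, and Supplementary Table 1 shows no new suicidality in any arm.

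**The case against.** The strongest reply is that the clause was probably meant for the gap before the allocated condition begins, and that little depends on it. Much of this stands:

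- The item 9 alert in Section 7 goes to the patient's own centre, for a call by the coordinator and site lead, in every arm.
- The synopsis makes clinically relevant suicidal ideation an obligatory reason for discontinuation, so that step does not wait for the review in Section 8.1.
- SAE sheets, the second-visit assessment and German-site monitoring continue. The suicidality SOP is in an appendix not shown and may include central notification.
- Section 9.3 calls itself information for the investigator and leaves duties to authorities untouched.

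The intended reading may be the narrow one, but no text says so, and the protocol's use of the word treatment points the other way.

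Several stronger readings are tempting, and the documents do not support them:

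- **That an exempt SAE is reported only a year later.** The AE deadline is "Upon completion of patient follow-up", and Section 6.6 gives "Duration of follow-up: 1 year after study inclusion". But nothing says an exempt SAE reverts to the AE deadline, so no delay can be calculated.
- **That the monitoring committee sees only the active arms.** Section 9.4 has it assess safety data regularly, and neither table in Section 9.3 names it as a recipient. Its data route is unstated for every arm.
- **That the earlier MS trial shows ideation arising in the waitlist arm.** Section 5.1.1 gives waitlist counts of 1 before and 1 after on BDI item 9, and 4 before and 3 after on SBQ-R item 4. The active arm had 2 on SBQ-R item 4 at baseline. No new ideation was seen in either group, and SBQ-R item 4 is not an SAE criterion here, so these counts cannot be scaled to expected SAEs.
- **That waitlist adverse events went unrecorded.** SAP Section 5.4 tabulates events by group, and Supplementary Table 1 lists control events: 3 worsening of depressive symptoms and 6 other.

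**Conclusion.** The defect is real but minor. On the literal text, the 15-day SAE report to the principal investigator does not apply to the waitlist arm through the 12-week comparison and on to month 6, while it applies to both active arms. That conflicts with Section 8.1 and makes central reporting unequal by arm. Any effect on the monitoring committee's comparison of arms is conditional on its using these reports.

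The conclusion rests on two things: treatment meaning the programme, as the synopsis and Section 7 use it, and the 6-month wait. If the sponsor meant the start of the allocated condition, the gap closes, but the protocol has to say so. No harm to any patient is shown, and local safety handling and the reported results are not called into question.

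**What to change.** In Section 9.3, limit the first exception to SAEs that occur before randomization, and state that the report chain covers all three arms from randomization with the existing 15-day deadline. In Section 9.1, define an adverse event as an untoward occurrence after randomization in any arm, whether or not the programme is in use.

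The cost is a wording amendment to two sections and an SAE form for probably very few waitlist events. AEs and SAEs are already collected at weeks 4, 8 and 12 and at months 6 and 12, so no visit, assessment or patient is added.

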### Principal Investigator Reporting Duties

The principal investigator documents every reported SAE. The principal investigator furthermore reports every SUSAR immediately, in any case within 15 days after it became apparent, to the participating investigators. A lethal or life-threatening SUSAR is reported immediately, in any case within 7 days after it became apparent, to the participating investigators. A follow-up report within further 8 days can be transmitted if information retrieved was initially incomplete.

All data will be transformed in pseudonymized form.

#### **9.4 Data Monitoring Committee (DMC)**

The DMC is an independent committee regularly assessing safety data during the course of this study. Primary interest of the DMC is the safety of trial participants and integrity and validity of collected data. The DMC reviews frequency and severity of SAEs. It states a recommendation to the principal investigator whether to continue or discontinue trial conduction. Details on the predefined criteria are given in Chapter 12.5.3.

Members of the DMC are

**[name]**, M.D., Brigham and Women's Hospital, Harvard Medical School, Boston, USA

**[name]**, M.D., Asklepios Clinic Tiefenbrunn, Germany

## 10 Documentation

### 10.1 Case Report Form (CRF)

Acquired data is documented in paper CRF as well as eCRFs (IDEMS study platform). A copy of the paper CRF can be found in the appendix.

### 10.2 Investigator Site File (ISF)

All essential documents according to ICH GCP Chapter 8 are filed in the Investigator Site File on site.

### 10.3 Trial Master File (TMF)

All essential documents according to ICH GCP Chapter 8 are filed in the Trial Master File at the coordinating centre (NCRC).

## 11 Quality Management

### 11.1 Assessment of trial conduction and data quality

Indicators of quality for trial conduction are

- Adherence to recruitment rate
- Adherence to selection criteria
- Adherence to per-protocol-treatment
- Adherence to visit schedule

#### 11.1.1 Monitoring

Internal Monitoring for German sites will be conducted by the coordinating centre / principal investigator. Every patient will be monitored for selection criteria and informed consent. Internal monitoring will also verify if appropriate SOPs were followed in case an SAE (suicidal ideation or intent) occurred. The investigator assures complete and unrestricted access to study data for the monitor. Monitoring details will be fixed in a monitoring manual.

Most of the data will be directly entered to the electronic study platform (mostly be the participant) or CRF and are thus considered source data.

#### 11.1.2 Audits / Inspections

No internal audits are planned, but the Principal Investigator reserves the right to initiate a previously not planned audit.

### 11.2 Standardization and Validity

All rating scales have previously been standardized and validated.

## 12 Data Management

All personalized data is acquired in a pseudonymized manner. Every patient is attributed a unique ID in the course of inclusion. The investigator keeps a confident list containing full patient name and attributed ID. This list is accessible only to the local study team and monitors. Source data files are accessible to monitors, auditors and inspectors.

### 12.1 Data Acquisition and CRFs

Acquisition is performed using *paper Case Report Forms (CRF)*, distributed by the sponsor. Additional data are acquired in the study platform.

The original is intended for the principal investigator/coordinating study center, a copy remains on the local site. Forms have to be completed with a pen, use of pencils is not permitted. Corrections have to

be done as follows: any mistake is crossed out by a single line, correct information is written next to it, dated and signed by the investigator and ideally a reason for correction is given. If missing information prohibits completion of a field, an explanation should be given.

## 12.2 Data Processing

For paper CRFs, the principal investigator/coordinating centre transposes data to a digital format. Data will be checked for range, validity and consistency. Implausible or missing data can be corrected in accordance with the investigator, documentation of correction is stored along with the CRFs. Validated data is stored in a database. At the end of the trial official database closure is documented. For evaluation of data we intend to use the current version of SPSS.

## 12.3 Creation of Pseudonym

Patients will be incrementally numbered based on date and time of inclusion. The number consists of a letter referring to the site of inclusion (B=Berlin, H=Hamburg, P=PennState, K=Kansas City, L=Los Angeles) and four patient-related digits (i.e. the first patient in Berlin will receive the code "B0001").

## 12.4 Randomization

The trial will use a central, web-based randomization tool built into the study platform. Randomization will be conducted through this online system, ensuring concealed allocation. Patients will be randomized 1:1:1 to one of the three trial arms (no blocking, no stratification). To ensure concealed allocation, eligibility will be determined and all baseline assessments completed before randomization in compliance with CONSORT guidelines (extended CONSORT Statement to Randomized Trials of Non-pharmacological Treatment (27) and CONSORT Statement for eHealth (28)). Group assignment will be communicated automatically by a webmessage in the study platform. The clinicians and raters who will be conducting clinical assessments (structured interviews) will be blind to treatment assignment (single blind RCT).

### Sample size estimation

A sample size of 100 patients per intervention group gives a conjunctive power (probability of rejecting both null hypotheses comparing Deprexis and DeprexisPlus to waitlist control) of 90% for a Dunnett test at the usual one-sided significance level of 2.5% assuming standardized mean differences of 0.5 for Deprexis vs. WLC and 0.8 for DeprexisPlus vs. WLC in the primary outcome change in BDI from baseline to week 12. Adjusting for 20% dropout we aim to recruit 125 patients per group resulting in a total sample size of 375 patients. The power was simulated with 10,000 replications using EAST 6.3.

## 12.5 Statistical Evaluation

Statistical analysis will be conducted in accordance with the following guidelines of the International Conference on Harmonization (ICH):

- ICH E3: Structure and Contents of Clinical Study Reports
- ICH E6: Good Clinical Practice (GCP). Consolidated Guideline
- ICH E9: Note for Guidance on Statistical Principles in Clinical Trials

### 12.5.1 Hypotheses

**Primary hypothesis:** All analyses will be conducted as intention-to-treat (ITT). To definitively test the effectiveness of Deprexis for reducing depressive symptoms in MS at the end of treatment, the primary outcome change in BDI from baseline to week 12 will be analyzed by means of linear mixed effect models for repeated measures adjusted for baseline measurements with fixed effects for intervention, center, time and baseline BDI score, and random subject effects for individual patients including all patients with at least one post-baseline measurement (29). Least squares means will be reported for the intervention groups with 95% confidence interval (CI) as well as the difference between the least squares group means with 95% CI. Deprexis vs. WLC and DeprexisPlus vs. WLC will be tested by a Dunnett test controlling the familywise type I error rate at the level of 2.5%

(one-sided). *The primary hypothesis will be tested in a confirmatory manner.* In a secondary step, we will determine the added value of therapist email support Deprexis vs. DeprexisPlus at a two-sided level of 5%, if efficacy of Deprexis and DeprexisPlus for reducing depressive symptoms in MS could be demonstrated.

**Secondary hypotheses:** The analyses of secondary and tertiary endpoints (such as BDI-FS, QoL, cognitive function and fatigue scales) will follow the same approach as the analyses described for the primary endpoint. The proposed trial will create a large data set from n=400 MS patients and followed for 12 months that will enable us to gain valuable insight into the potential predictors, confounders, intermediates in the causal pathway, and interactions of Deprexis(Plus) treatment effects. In supporting exploratory analyses we will investigate potential moderators of treatment effects by including these and their interaction with treatment in the linear mixed effects models described above. Potential moderators include disease-modifying therapies (DMTs), level of disability at baseline (as measured by Disease Steps and patient-rated EDSS), cognitive status at baseline (as measured by BICAMS), and level of fatigue at baseline (as measured by the FSMC).

### 12.5.2 Evaluation of primary endpoint

Primary hypothesis is tested in a confirmatory manner:

All analyses will be conducted as intention-to-treat (ITT). The specific statistical analyses for each aim are as follows: **Aim 1:** To definitively test the effectiveness of Deprexis for reducing depressive symptoms in MS at the end of treatment, the primary outcome change in BDI from baseline to week 12 will be analyzed by means of linear mixed effect models for repeated measures adjusted for baseline measurements with fixed effects for intervention, center, time and baseline BDI score, and random subject effects for individual patients including all patients with at least one post-baseline measurement (29). Least squares means will be reported for the intervention groups with 95% confidence interval (CI) as well as the difference between the least squares group means with 95% CI. Deprexis vs. WLC and DeprexisPlus vs. WLC will be tested by a Dunnett test controlling the familywise type I error rate at the level of 2.5% (one-sided). **Aim 2:** To determine the added value of therapist email support Deprexis vs. DeprexisPlus will be tested at a two-sided level of 5%, if efficacy of Deprexis and DeprexisPlus for reducing depressive symptoms in MS could be demonstrated. **Aim 3:** To explore the long-term stability of therapeutic effects (12 months) and the potential of a booster session to enhance maintenance, we will conduct similar linear mixed effect models for repeated measures in a two group comparison (Booster condition vs No Booster) during the extension phase (i.e. from week 12 (V2) to the end of the trial (month 12) accounting for the intervention (Deprexis or DeprexisPlus). Here, we will only include patients who had originally been randomized to either Deprexis or DeprexisPlus in primary trial phase.

**Missing data:** Although the mixed models described above are robust to a certain extent to missing data, sensitivity analyses will be performed as supporting analyses, if missing data are substantial and suspected to be due to dropout. Models that can account for informative dropout such as shared random effects models will be employed to explore the sensitivity of the analyses to certain dropout mechanisms (30). Standard procedures for reporting of adverse events will be used. Adverse events will be summarized as frequencies and percentages by intervention group. No interim analyses are foreseen. The ITT population as well as all other details will be defined in the Statistical Analysis Plan, which will be finalized before database lock.

